## 5 TRIAL FLOW CHART

[figure not shown]

## 6 INTRODUCTION

### 6.1 Background

Minimal Change Disease (MCD) and Focal Segmental Glomerulosclerosis (FSGS) are auto-immune renal diseases that present with a common clinical phenotype, the nephrotic syndrome (NS), characterised by heavy proteinuria and debilitating oedema. When nephrotic, patients require frequent hospital admissions; infections and venous thrombo-embolism are common and can be fatal. With treatment, patients with MCD usually have preserved renal function, however, those with FSGS frequently still progress to end stage kidney disease (ESKD), requiring renal replacement therapy (RRT). Patients with FSGS and NS have five year renal survival rates (without dialysis or transplantation) of 60-90% and ten year renal survival rates of 30-55%. 10 year survival improves to 80% if remission from proteinuria is achieved.

Primary MCD and FSGS are rare, affecting about 10/million population/year. Together they are now responsible for 50% of adult idiopathic NS presentations. MCD and FSGS are historically described as two separate disease entities. However, emerging data indicate that they are part of a disease continuum^6. Both conditions are characterised by electron-microscopic evidence within the glomerulus of diffuse effacement of podocyte foot processes, resulting in a severe functional defect in selective permeability. In FSGS, there is additional focal (i.e. in some areas of the kidney cortex) and segmental (segments of the glomerulus are affected) fibrosis and occlusion of the glomerular capillaries. It is notable that, in FSGS, glomeruli not displaying segmental lesions demonstrate the classical features of MCD at electron microscopy.

| RELATIVE FREQUENCY (%) OF PRIMARY GLOMERULAR DISEASE
UNDERLYING NEPHROTIC SYNDROME |                                 |                                 |                                 |
|-----------------------------------------------------------------------------------------------|---------------------------------|---------------------------------|---------------------------------|
| Disease                                                                                | 1960s and 70s            |                                 | 1990s to the
present |
|                                                                                               | Adults
< 60 years | Adults
> 60 years |                                 |
| Focal Segmental Glomerulosclerosis (FSGS)                                                     | 15                              | 2                               | 35                              |
| Minimal Change Disease (MCD)                                                                  | 20                              | 20                              | 15                              |
| Other glomerular disease                                                                      | 65                              | 78                              | 50                              |

*Adapted from Hull and Goldsmith*

The aetiology of primary MCD and FSGS has not been completely delineated. However, there is strong evidence of a circulating factor, or factors, in MCD and FSGS. Definitive evidence of a circulating factor is provided by the recurrence of NS following kidney transplantation in 20-30% of patients with FSGS. It is likely that circulating factors are released by immune cells, particularly at the time of intercurrent infection. Several other strands of evidence support the view that MCD and FSGS have an immune aetiology. Both diseases respond to immunosuppression with glucocorticoids. There is evidence for T cell involvement: in children with idiopathic NS regulatory T-cell numbers were reduced and cytokine profiles altered during relapse. In a rat model of FSGS, transfer or induction of regulatory T-cells results in disease attenuation. B cells have also been implicated: increased B cell numbers were present in the kidneys of children with FSGS compared with mesangiocapillary glomerular nephritis MCGN (another kidney disease characterised by proteinuria) . In a murine model, transfer

of glomerular antigen-specific B cells induced glomerular injury and proteinuria. This effect was mediated by IL-4, as transfer of IL-4-deficient B cells did not induce proteinuria. Overexpression of IL-4 in mice was sufficient to induce kidney injury and proteinuria and could be attenuated by JAK kinase inhibitors. In kidney biopsies of patients with MCD, STAT6 activation (induced by IL-4) was increased, suggesting IL-4 exposure in these patients. These data also suggest that the role of B cells in NS could be mediated by cytokines.

Thus existing evidence supports the hypothesis that MCD and FSGS represent manifestations on a disease continuum, and are likely to have an auto-immune aetiology. Given that existing treatments overlap, this trial addresses MCD and FSGS as a single disease entity.

## 6.2 Clinical data

There is a paucity of evidence to support existing treatments for MCD/FSGS. The Kidney Disease Improving Global Outcomes (KDIGO) recommendations concludes that no evidence graded higher than 'C' exists for the treatment of these diseases in adults.

### 6.2.1 *Glucocorticoids*

Glucocorticoids are the mainstay of treatment in MCD/FSGS, with MCD typically responding faster than FSGS. Response rates are higher in MCD at 90%, compared to those in FSGS at 40-80%. In steroid responsive patients with both diseases, recurrent relapses occur in 75% when the steroid dose is reduced or withdrawn. These frequently relapsing (FR) or steroid dependent (SD) patients accrue a high steroid exposure over time, with weight gain, diabetes, infection and osteoporosis. In patients with FSGS, renal function deteriorates if long term remission of proteinuria cannot be achieved. In one retrospective analysis (n=197), 23% (n=45) progressed to dialysis after a median follow-up of 1.8 years from the time of renal biopsy diagnosis. Achieving remission is very important for avoiding ESKD – in a cohort study of 281 patients with nephrotic FSGS, achieving at least partial remission was associated with markedly improved renal survival with a hazard ratio of 0.48 (95% confidence interval 0.24-0.96;p=0.04). ESKD is associated with poor quality of life and a risk of death exceeding most cancers and is expensive for the NHS.

### 6.2.2 *Other immunosuppression: cyclophosphamide calcineurin inhibitors (CNIs) and mycophenolate mofetil (MMF)*

Due to the morbidity of prolonged/repeated course of steroids, steroid sparing agents are regularly used in MCD/FSGS. Cyclophosphamide is thought to be most effective at maintaining remission in SD/FR MCD/FSGS, but the severe cumulative toxicity precludes long term use. CNIs are also effective at maintaining remission. In an open-label prospective cohort study of 26 adults with FR or SD NS, tacrolimus was as effective as cyclophosphamide at inducing and maintaining remission at 2 years. However, relapse rates are high on stopping therapy, so repeated prolonged courses are often required for many years. CNIs themselves are nephrotoxic, and patients require long term follow up with close monitoring of levels in the clinic for the duration of their therapy. In an open-label prospective cohort study, 12 adult patients with SD MCD were treated with tacrolimus therapy. The authors reported complete remission in 10 patients and partial remission in an additional patient. During a mean follow-up period of 24 months, 50% experienced relapse. In a small trial in children with steroid resistant NS, Choudhry and colleagues randomised 41 patients to tacrolimus or cyclosporine. Remission occurred in 85.7% and 80% of patients treated with tacrolimus and cyclosporine respectively, although relapses were more common in the cyclosporine group.

Mycophenolate is also used in clinical practice as a steroid sparing agent for patients with SD/FR MCD/FSGS. However there is little evidence to support this - in a Randomised Controlled Trial (RCT) by Gipson et al, mycophenolate was combined with high dose steroids in the form of dexamethasone. In this trial of 138 children and young adults with relapsing FSGS, cyclosporine was compared to dexamethasone and MMF and showed no significant difference in remission rates between trial arms (cyclosporine 46%, mycophenolate and dexamethasone 33%). The efficacy of using MMF alone instead of steroids is not clear.

### 6.2.3 *Rituximab*

Rituximab is a monoclonal antibody that targets and depletes B cells via CD20. It is a licensed treatment for other auto-immune diseases, rheumatoid arthritis and antineutrophil cytoplasmic antibody (ANCA) associated vasculitis, where it has an excellent safety profile. In a recent pooled analysis of 3,194 patients with rheumatoid arthritis exposed to 11,962 patient years of rituximab, serious infections occurred at a rate of 3.94 per 100 patient years (comparable to both methotrexate and placebo). Importantly, the risk of serious infections was stable over time, even with multiple courses of treatment. Opportunistic infections were very rare, and only two cases of pulmonary tuberculosis occurred. Rates of viral infections, including herpes zoster reactivation (9/1000 patient years), were low. Rituximab may therefore be considerably safer than existing treatments for MCD/FSGS.

As the pathogenesis of MCD/FSGS is not fully understood, the mechanism of action of rituximab is debated. Rituximab may exert its effect in MCD/FSGS through targeting B cells, but there is evidence that rituximab may prevent podocyte apoptosis by binding directly to podocyte sphingomyelin phosphodiesterase acid-like 3b (SMPDL-3b) and stabilising the cytoskeleton although the clinical impact of this observation is uncertain.

Randomised trial evidence to support the use of rituximab in MCD/FSGS is limited to paediatric studies. Here, NS is almost always due to MCD/FSGS, and kidney biopsy is rarely done. Instead, patients are treated on the basis of their clinical presentation with SD/FR NS. Ravani et al randomised 54 children with SDNS in an open-label non-inferiority design to receive rituximab and reduced dose steroid and cyclosporine, or standard steroid and cyclosporine doses. Proteinuria was lower after 3 months in the rituximab arm, and relapses occurred in only 18.5% of the rituximab arm compared with 48% in the control arm ( $p=0.029$ ). Notably, the probability of being drug free at 3 months were 62.9% and 3.7%, respectively ( $p<0.001$ ). In a double-blind randomised trial, Iijima and colleagues randomly assigned 48 children with SDNS to rituximab or placebo. Patients in the rituximab arm demonstrated a 50% increase in the median time to relapse ( $p=0.0001$ ). In a further non-inferiority open-label randomised trial, Ravani et al assigned 30 children with SDNS to receive either continued steroid therapy or a single IV infusion of rituximab. After 3 months, proteinuria was 42% lower with rituximab than control. The median time to relapse with rituximab was 18 months, whereas 14/15 control patients relapsed within 6 months. Several observational cohort studies in children support the findings from the above randomised trials.

Evidence to support the use of rituximab in adults with MCD/FSGS is more limited, but several observational studies have reported encouraging results. In a series of 17 adult patients with SD or FR MCD treated with rituximab, 11 patients remained relapse free (median follow-up 27 months), of whom 9 discontinued all immunosuppression. In another series of 41 adult rituximab treated patients with SD or FR MCD, complete remission was achieved in 25 and

partial remission in a further 7 patients. After a median follow-up of 39 months, 18 responders had experienced a relapse (mean time to relapse 18 (3-36) months). Thirteen of 17 patients retreated with rituximab again achieved remission. A prospective study of 25 adult patients with SD or FR MCD identified only 4 relapses within 12 months of rituximab treatment, and a reduction in the maintenance steroid dose in most patients. Papakrivopoulou et al reported a reduction in the frequency of relapse from 2.9 to 0.4 per patient year after treating 15 adult patients with SD or FR MCD with rituximab. In a series of 8 SD or FR FSGS adult cases treated with rituximab, 5 patients demonstrated no response. The three responders received higher doses of rituximab, suggesting that non-responders may have been under-treated. Ruggenti describes a cohort of 30 patients (10 children and 20 adults) with SD/FR NS secondary to MCD/FSGS and mesangiocapillary glomerulonephritis (MesGN). Nineteen patients had MCD, 8 FSGS and 3 MesGN. Following treatment with rituximab, the number of relapses fell from 88 in the year prior to rituximab to 22 during 1 year of follow up  $p < 0.001$ . This reduction in relapse risk was significant when children and adults, and MCD/MesGN and FSGS patients were considered separately.

## **7 RATIONALE FOR TRIAL**

### **7.1 Clinical need**

MCD/FSGS are rare auto-immune kidney diseases. Untreated, they result in considerable morbidity including kidney failure and death. Current treatments have serious limitations: whilst glucocorticoids are effective in the majority of patients, repeated courses are usually required, and the side effect burden of cumulative steroid exposure itself carries extensive morbidity and mortality for patients. In other autoimmune diseases where immunosuppression is required, steroid sparing regimens (including the use of biologics) are now the norm. In MCD/FSGS there is an urgent need for such steroid sparing regimes, that are both effective and safe, and do not adversely affect kidney function. Rituximab is the most promising candidate treatment. Indeed, it is currently used where other treatments have failed, or where the risk of toxicity from existing treatments is deemed unacceptably high. However, such use lacks supporting evidence from robust interventional trials, leading the KDIGO expert group to identify trials with rituximab in adults with MCD/FSGS as a key research priority. Given pressures on healthcare resources, studies assessing both the efficacy and cost-effectiveness of rituximab as treatment for MCD/FSGS within the context of the NHS are urgently needed.

### **7.2 Financial considerations**

MCD/FSGS often affects patients younger than 65 years, when they are economically active. The symptoms of NS and the requirement for hospital-based treatment result in time off work and loss of income. Complications arising from the disease or its treatment, such as serious infections, may require further hospital admissions. Loss of kidney function can result in ESKD requiring dialysis at great cost. Indeed, glomerulonephritides account for 18.9% of patients requiring RRT, and this is higher in those under 65 years of age (21.3%). Although MCD/FSGS make up only a proportion of this number, treatments that delay the onset of ESKD should result in a significant cost saving. Currently, patients are treated with multiple courses of a variety of different immunosuppressants over many years or even decades in an effort to reduce steroid exposure. Even if these treatments are successful in a steroid sparing capacity, they have significant toxicity themselves - oral cyclophosphamide in particular carries a high

risk of leucopenia and sepsis. There is a clear need for alternative effective treatment such as rituximab for MCD/FSGS. Given that rituximab is now off patent and biosimilar preparations are available, the cost of rituximab is likely to reduce further. TURING is therefore designed to assess the efficacy, safety, cost and cost effectiveness of rituximab at inducing sustained remission in patients with NS caused by primary MCD/FSGS.

## **8 TRIAL DESIGN**

### **8.1 Statement of design**

This is a randomised, two-arm (1:1 ratio), double blind, placebo controlled phase III trial to assess the efficacy, safety, cost and cost-effectiveness of rituximab in treating *de novo* or relapsing NS in patients with MCD/FSGS.

In addition to the main phase of the trial, the participating Renal Units will also offer the Open Label Phase to the participants on the placebo arm who relapse after achievement of partial or complete remission.

### **8.2 Number of centres**

We plan to include approximately 40 UK Renal Units within this trial; however we may increase the number of centres if required in order to recruit the required number of participants.

### **8.3 Number of participants**

We plan to randomise approximately 130-150 participants in this trial. Please see Section 16.2 Number of patients to be enrolled for details.

### **8.4 Participants trial duration**

Participants will have a minimum of 24 months follow up from Day 0 (Start of Protocolised Prednisolone Regimen) unless a partial remission is not achieved at week 16 or the primary outcome measure event is observed earlier (see section 11.6 end of trial visit). Participants who achieve the primary endpoint and subsequently enter the Open Label Phase (OLP) will have a minimum of 26 weeks follow up in the OLP.

All participants in whom the primary outcome measure event is not observed will remain in the trial, in follow-up for a minimum of 24 months.

All participants will return to their standard of care after end of trial participation.

### **8.5 Trial objectives**

#### **8.5.1 Primary objective:**

- Assess the efficacy of rituximab on the time from partial / complete remission to relapse of NS.

### 8.5.2 Secondary objectives

- Assess the effect of rituximab on NHS and societal resource use and hence cost.
- Assess the effect of rituximab on safety and on secondary measures of efficacy, such as achievement of partial and complete remission of NS and the preservation of renal function.
- Assess the effect of rituximab on health status of participant.

### 8.5.3 Exploratory objective

- To explore the interaction between age of onset with the efficacy of rituximab.
- To explore efficacy of delayed rituximab in nephrotic syndrome (data from OLP)

## 8.6 **Trial outcome measures**

### 8.6.1 Primary outcome measure

Primary outcome measure: Time from partial or complete remission (whichever documented first) to relapse of NS as defined below (Appendix 6):

- COMPLETE REMISSION (CR): PCR<50mg/mmol (only one result required).
- PARTIAL REMISSION (PR): Reduction in Urinary PCR  $\geq$  50% from Day 0 - Start of Protocolised Prednisolone Regimen (SPPR) AND PCR  $\geq$  50mg/mmol and  $\leq$  300mg/mmol on two consecutive results (performed within 14 days of each other). The date of first assessment is the date of partial remission.
- RELAPSE: recurrent NS as defined by albumin < 35 g/l, PCR > 300mg/mmol and an increase in 100% over the nadir value during remission on two consecutive results (performed within 14 days of each other). The date of first assessment is the date of relapse. For patients with an albumin  $\geq$  35g/l prior to relapse, only one PCR result is required (i.e. PCR > 300mg/mmol that has risen by 100% over the nadir value and an albumin < 35g/L).

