#### 11.5.1 Week 16 Visit

Patients who have not responded to treatment by achieving partial or complete remission at the week 16 visit (16 weeks from Day 0, +/- 1 week) will leave the trial and return to standard of care treatment. These patients will not receive the third dose of rituximab or placebo at week 26 as they have not demonstrated steroid responsiveness, and on-going treatment with prednisolone with or without rituximab is likely to be futile.

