## 14 **EVALUATION OF RESULTS (Definitions and response/evaluation of outcome measures)**

### 14.1 **Definitions of Remission and Relapse**

Primary outcome measure: Time from partial or complete remission (whichever documented first) to relapse as defined below (see appendix 6):

- COMPLETE REMISSION (CR): PCR < 50mg/mmol (only one result required).
- PARTIAL REMISSION (PR): Reduction in Urinary PCR  $\geq$  50% from Day 0 - Start of Protocolised Prednisolone Regimen (SPPR) AND PCR  $\geq$  50mg/mmol and  $\leq$  300mg/mmol on two consecutive results (performed within 14 days of each other). The date of first assessment is the date of partial remission.
- RELAPSE: recurrent NS as defined by albumin < 35 g/l, PCR > 300mg/mmol and an increase in 100% over the nadir value during remission on two consecutive results (performed within 14 days of each other). The date of first assessment is the date of relapse. For patients with an albumin  $\geq$  35g/l prior to relapse, only one PCR result is required (i.e. PCR > 300mg/mmol that has risen by 100% over the nadir value and an albumin < 35g/L).

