## 25.6 Appendix 6 – Primary Outcome Measure Events

|                                          | Pre Achieving Complete/Partial Remission |                                                                                       |                                  | Post Achieving Complete/Partial Remission                         |                                          |                                    |
|------------------------------------------|------------------------------------------|---------------------------------------------------------------------------------------|----------------------------------|-------------------------------------------------------------------|------------------------------------------|------------------------------------|
| PCR level                         | PCR≤50mg/mm
ol                        | 50<PCR≤300 mg/mmol                                                                    |                                  | PCR>300 mg/mmol                                                   |                                          |                                    |
| PCR change from baseline or nadir |                                          | PCR reduction from baseline ≥50%                                                      | PCR reduction from baseline <50% | PCR increase from nadir value >100%                               |                                          | PCR increase from nadir value 100% |
| Albumin level                     | Any                                      | Any                                                                                   |                                  | Albumin<35g/l                                                     | Albumin≥35g/l                            |                                    |
| No. of PRC assessments required   | One                                      | Two consecutive (within 14 days of each other)                                        | Any                              | Two consecutive (within 14 days of each other)                    | Any                                      | Any                                |

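### A confirming PCR below 50 mg/mmol forfeits the partial-remission date: remission is dated up to 14 days later and, near week 16, an improver can be read as a treatment failure

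*Protocol*

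**What the plan says.** Sections 8.6.1 and 14.1 of the protocol define partial remission as at least a halving of urinary PCR from Day 0 together with a band on two samples: "AND PCR $\geq$ 50mg/mmol and $\leq$ 300mg/mmol on two consecutive results". Timing and dating follow: "300mg/mmol on two consecutive results (performed within 14 days of each other). The date of first assessment is the date of partial remission".

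Complete remission needs one sample: "COMPLETE REMISSION (CR): PCR<50mg/mmol (only one result required" in 8.6.1, and likewise "COMPLETE REMISSION (CR): PCR < 50mg/mmol (only one result required" in 14.1. The primary clock is "Time from partial or complete remission (whichever documented first) to relapse of NS as defined below (Appendix 6".

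Appendix 6 tabulates partial remission as "50<PCR≤300 mg/mmol", with the number of assessments given as "Two consecutive (within 14 days of each other".

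Section 11.5.1 acts on the result: "Patients who have not responded to treatment by achieving partial or complete remission at the week 16 visit" leave the trial, the visit being 16 weeks from Day 0 with a window of 1 week either side. Section 11.5 lets the procedures of a pre-remission visit spread over two weeks. Section 11.14 dates such a spread visit by its laboratory samples.

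**The concern.** The lower limit of 50 mg/mmol separates partial from complete remission. Applied to the confirming sample, it also decides which date counts. Only partial remission is dated back to the first sample; complete remission takes the date of its own single sample. A participant who improves between the two samples is therefore treated less favourably than one who does not.

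Two things are at stake. First, the start of the primary time-to-relapse clock, and the secondary time from Day 0 to remission, move later in participants who remit fastest. Second, around week 16 the shift can change status as well as date. A participant classed as not in remission has a final visit at week 16 (11.12), gets no third dose (11.5.1), cannot enter the open label phase (10.2), counts as a treatment failure (8.6.2) and enters the absorbing state of the response-function analysis (16.1.2). Sites act on the definition at week 16, so a later analysis plan cannot restore the lost follow-up.

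**Working it through.** The protocol gives no figure on this point to reproduce, so the check applies the rules literally to example pairs.

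**Inputs.** The remission rules are those of 8.6.1. Week 16 is day 16 × 7 = 112, and its window in 11.5.1 is days 105 to 119. The planning medians in 16.2 are 9 and 18 months. A Day 0 PCR of 600 mg/mmol is assumed for illustration, so the 50% criterion is met at 300 or below.

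**Step 1: classification of pairs taken within 14 days.**

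| First PCR | Confirming PCR | Partial remission? | Complete remission? | Remission dated |
|---|---|---|---|---|
| 200 | 250 (reduction 350/600 = 58%) | yes | no | first sample |
| 200 | 60 | yes | no | first sample |
| 200 | 40 | no, second value below the band | yes | second sample |

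**Step 2: size of the date shift.** The shift equals the gap between samples, at most 14 days. 14 / 30.4375 = 0.46 months. Relative to the planning medians this is 0.46 / 9 = 5.1% and 0.46 / 18 = 2.6%.

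**Step 3: status at week 16 for the pair 200 then 40.** The participant is a remitter only if the day of the first sample plus the gap does not exceed the cut-off. The protocol does not settle the cut-off, so three are shown: day 112 (nominal), day 119 (end of window) and day 126 (day 112 plus the 14-day confirmation period).

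| First sample | Cut-off day 112 | Cut-off day 119 | Cut-off day 126 |
|---|---|---|---|
| day 98 | remitter, all gaps | remitter, all gaps | remitter, all gaps |
| day 105 | remitter if gap ≤ 7 days | remitter, all gaps | remitter, all gaps |
| day 112 | failure, any gap | remitter if gap ≤ 7 days; failure if 8 to 14 | remitter, all gaps |
| day 119 | failure, any gap | failure, any gap | remitter if gap ≤ 7 days; failure if 8 to 14 |

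The pair 200 then 60 with a first sample on day 112 is partial remission dated day 112 for every gap up to 14 days, and so meets all three cut-offs. With a day 119 limit, a confirming sample on days 120 to 126 makes the participant at 60 a remitter and the participant at 40 a failure. (A first sample on day 119 misses a day 112 cut-off whichever way the second moves.)

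**Step 4: how many participants.** The protocol gives no PCR trajectories. An illustrative simulation assumed a repeat PCR 7 to 14 days after every in-band value, a PCR half-life of 0.7 to 2.5 weeks, within-patient CV of 30 to 50% and a mean response lag of 5 weeks. It put 1.1 to 1.9% of randomised participants in the week 16 group: 0.011 × 130 = 1.4 to 0.019 × 150 = 2.9, or about 1 to 3 people. It dated remission 1 to 2 weeks later in 9 to 23%. None of these inputs is in the protocol. The week 16 count is towards the upper end, because it includes every repeat below 50 after an in-band week 16 value, even one taken within 7 days and so still inside the window.

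**Step 5: a PCR of exactly 50.** Sections 8.6.1 and 14.1 place 50 in partial remission (at or above 50) and reserve complete remission for values below it. Appendix 6 starts partial remission above 50 and puts 50 itself in complete remission. The same single value thus needs confirmation under one text and not under the other.

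**The case against.** The strongest reply is that complete remission catches the improver. One PCR below 50 suffices and the clock starts at whichever remission is documented first, so at visits well before week 16 the participant is still a remitter. This stands, and it limits the usual effect to a shift of at most 14 days. That is shorter than the 4-weekly visit spacing in 14.2, and no difference between arms has been shown.

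A second reply is that partial remission first seen at week 16 cannot be known until the repeat is back. A site must already wait for that sample and could sensibly accept complete remission shown on it. That reading is reasonable, and 11.5 offers some support by letting procedures run over two weeks. However, 11.14 dates a visit by its samples and 11.5.1 gives a window of 1 week, so the text does not secure this reading. What stands is that failure at week 16 follows from a literal reading and is not the only possible one.

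A third reply is that mixed pairs are a derivation detail for the analysis plan. This holds for the date. It does not hold for week 16 status, which is decided at site and ends follow-up.

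**Conclusion.** The point holds as a minor defect in the endpoint definition. The rule as written dates a better course later than a worse one, by up to 14 days. In a narrow band of timing around week 16 it can, read literally, reverse remitter and failure. The direction follows from the wording alone; the frequency does not, and is probably small. No sample size, power or alpha figure changes.

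A reader might infer three stronger things that the protocol does not support:

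- **Any participant who improves below 50 at confirmation is a non-remitter.** This requires a first qualifying PCR at or near week 16 and a repeat after the applicable cut-off.
- **The later date breaches the protocol's own dating rule.** The first-assessment rule is stated for partial remission only; dating complete remission at its own sample follows the text.
- **Such participants always drop out of the primary analysis.** Section 16.1.2 has two routes. A participant classed as a failure has no remission duration to contribute to the comparison among responders. The response-function route is based on the intention-to-treat population and counts week 16 failures in the absorbing state.

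**What to change.** In 8.6.1, 14.1 and Appendix 6, keep the first PCR at 50 to 300 mg/mmol with a reduction of at least 50%. Require the confirming PCR within 14 days only to be 300 mg/mmol or below with a reduction of at least 50% from Day 0, with no lower limit, and date remission at the first result. The pair 200 then 40 is then dated as 200 then 60 already is, and a first qualifying sample on day 112 gives remission dated day 112.

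In the same edit:

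- Reconcile the week 16 passages (11.5, 11.5.1 and 11.14) with the 14-day confirmation period, so that it is clear when status is fixed. Remission status also governs continued treatment, so which limit applies is for the trial team to settle.
- Reconcile the handling of a PCR of exactly 50 between 8.6.1, 14.1 and Appendix 6.

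No extra tests are needed. The cost is an amendment to the wording of the primary endpoint definition and to the derivation code. Remission dates can be re-derived from recorded PCRs, but the scheduled follow-up of anyone already withdrawn at week 16 under the current wording cannot be recovered.
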